## Abstract

This trial aims to investigate the effects of the ActTeens physical activity program, on adolescents’ physical activity level, health-related fitness, cardiometabolic and mental health. The trial will aim to recruit ~140 adolescents (aged 13–14 years). Participants will be randomized into either intervention or control groups. The intervention will be guided by social cognitive theory and self-determination theory and implemented over one school term (24-weeks). The *ActTeens Program* will include: (1) structured physical activity sessions delivered within physical education, including movement-based games and dynamic stretching warm-ups; resistance training skill development; high-intensity training workouts; and cool-downs; (2) self-monitoring plus goal setting for physical activity by pedometer-smart wearable; and (3) healthy lifestyle guidance (social support) by WhatsApp® messages about healthy eating and regular physical activity for the intervention and parents groups. Study outcomes will be assessed at baseline, 24-weeks from baseline, and 12-months from baseline. Physical activity (accelerometer) is the primary outcome. Secondary outcomes include muscular and cardiorespiratory fitness, cardiometabolic profile, and mental health. A process evaluation will be conducted (i.e., recruitment, retention, attendance, and program satisfaction). This project will have the potential to address many questions and debates regarding the implementation of physical activity interventions in low-and- middle-income countries.

**Trial registration:** ClinicalTrials.gov NCT05070377. Registered on 7 October 2021.

## Introduction

Participation in regular physical activity (PA) is associated with numerous health benefits, including improved cardiorespiratory fitness (CRF), body composition, cardiometabolic profile, and mental health [1, 2]. To achieve these health benefits, current national [3] and international [2] guidelines recommend children and adolescents participate in an average of 60 minutes daily of moderate to vigorous physical activity (MVPA) and engage in vigorous physical activity (VPA), muscle-strengthening [e.g., resistance training (RT)] and bone-strengthening activities three days a week. Unfortunately, evidence suggests that 81% of school-aged adolescents (11 to 17 years) across the globe are not meeting these recommendations [4], and in Brazil, only 8.4% of adolescents are sufficiently active [5]. Of additional concern, longitudinal studies have demonstrated that PA and health-related fitness (cardiorespiratory and muscular) levels decline during adolescence [6–8]. According to the Oliveira et al. [9], less than half of the evaluated Brazilian adolescents were classified with adequate level on the physical fitness tests (push-ups and PACER) by Fitnessgram criteria.

Previous studies [10, 11] have found that low CRF and muscular fitness levels are associated with a higher risk of developing various chronic diseases (high blood pressure, hyperglycemia, and dyslipidemia). In this perspective, Roldão da Silva et al., [12] founded an inverse association between the muscular fitness (curl-up and push-up) and CRF with the clustered cardiometabolic risk in Brazilian adolescents.

Furthermore, studies also show that PA [13, 14], CRF [15, 16] and muscular fitness [11] have been associated with mental health outcomes. These findings have important implications regarding the mental health of Brazilian adolescents, since, data from the Erica (Study of Cardiovascular Risks in Adolescents) reported a high prevalence (30.0%) of common mental disorders (symptoms of depression and anxiety) in the young population [17].

Importantly, physical fitness in childhood and adolescence has been considered a powerful predictor of health later in life [18] and adequate levels of PA are essential for the development and maintenance of health-related fitness. Consistent findings showed that a high level of MVPA was associated with better aerobic and muscular fitness in adolescents [19, 20].

The school environment is a context where young people spend much of the day learning about different topics, including health. As such, schools are a suitable setting to provide opportunities and to inform adolescents about the benefits of regular PA [21, 22]. The Physical Education (PE) classes can help adolescents to consolidate active lifestyle habits that will last across the life-span [21]. Moreover, this opportunity may expose adolescents to varying forms of PA that they may not have been exposed to outside of school.

Despite the potential for schools to influence students’ health behaviors, when exploring the existing literature, previous school-based PA interventions targeting adolescents have had mixed success [23, 24]. Borde and colleagues [24] suggest the effects of school-based interventions targeting adolescents have been trivial. Emerging evidence has identified that poor implementation of programs is a major barrier to the success of school-based interventions [25]. According to Beets et al [26], poor implementation is potentially due to program drift and voltage drop as interventions progress from evaluating efficacy and effectiveness to dissemination.

Research [27] has shown that multicomponent interventions (ie, comprehensive school-based PA programs) appear to be more successful than single-component interventions. Another specific component is social support provided by parents and friends, which are factors that influence the PA levels of adolescents and should be considered in adolescent intervention efforts [28, 29]. Moreover, another alternative strategy is to deliver digital programs (eHealth and mHealth), reviews [30, 31] show the potential of eHealth and mHealth interventions for changing adolescents’ activity behaviors in the short term, particularly when integrated with other intervention components (eg, school-based environmental changes).

Therefore, multicomponent interventions including strategies in the school environment, out-of-school, and parental involvement, have been effective to improve the PA levels [32, 33], physical fitness (cardiorespiratory, muscular) [34, 35], well-being [36], and reduction of the sedentary behavior [37, 38]. However, this evidence base was largely drawn from high-income country, with sparse representation of in low-and- middle-income countries (LMICs). Thus, more research that aims to develop, implement, and evaluate adolescent physical activity interventions considering the context-specific of the LMICs is necessary.

In Brazil, school-based programs [33, 39, 40] have been developed with a focus on the promotion of active behavior in teens, however, these programs only included strategies within the school context and with a predominant focus on the aerobic component of youth PA guidelines. Thus, considering PA benefits for health, knowing the need to develop strategies to encourage active behavior both in and out of school, and the scarcity of muscular fitness programs in schools, there is a need to implement PA integrated programs that provide new opportunities for practice in the school setting and promote an active lifestyle for adolescents.

### Study objectives

This paper describes the protocol for a randomized controlled trial testing a PA program- *ActTeens Program*- to improve the PA level, health-related fitness, cardiometabolic and mental health in adolescents.

The aims of the trial are to: 1) to investigate the impact of 24 weeks PA program on the PA level in adolescents; 2) to verify the effects of 24 weeks PA program on the CRF and muscular fitness, metabolic profile and mental health; and 3) to analyse the potential mediators of PA behaviour change. Finally, the ActTeens Program will undergo detailed process evaluation to determine if the program has been implemented as intended and verify possible factors influencing implementation.

## Materials and methods

### Study design

The trial is registered in the protocol of clinical trials of the National Institute of Health clinicaltrials.gov (NCT05070377) on 7 October 2021 and approved by the human research ethics committee of the States University of Northen of Parana, Brazil (n° 4.452.513). The present study was written following Standard Protocol Items: Recommendations for Interventional Trials (SPIRIT) [41], which was aimed to improve the quality of clinical trial (S1 Checklist). The intervention will be evaluated using a two-arm randomized controlled trial with intervention and usual practice control groups. The assessments will be conducted at baseline, after 24-Weeks (primary endpoint) and after 48-Weeks from baseline (secondary endpoint). Baseline data collection will occur in the school term preceding the intervention (March 2022). The intervention will take place from April to October in public schools in Jacarezinho City. Post-test data collection (ie, 6-month follow-up) will start at the end of October and it will continue until midway through November, with the final following assessments (i.e., 12-month follow-up) being completed in April 2023.

### School recruitment and selection

The secondary public schools in Jacarezinho City, including students from 13–14 years (i.e., Grade 8 and 9) will be eligible to participate. Schools will be recruited through a list provided by the Regional Education Center of Jacarezinho, Pr, regarding the 2022 academic year. Then, emails will be sent directly to eligible schools (school principals and Grade 8 and 9 coordinators). Once schools have expressed interest in the study, a member of the research team (project coordinator) will meet with the school representative(s) and explain the study requirements. At this time, each school will be asked to identify if grade 8 and 9 PE teachers are willing to facilitate the delivery of scheduled *ActTeens* sessions during their lessons.

### Participants

Physical Education teachers of the participating Grade 8 and 9 classes, as well deliver the program during the scheduled class time. Eligible participants will be grade 8 or 9 students aged between 13—and 14 years. Parental signed informed written consent will be obtained from students before participation. This consent authorizes the student’s involvement in the evaluation component of the study, as well as the authorized use of their de-identified data. Students with a cardiometabolic disease diagnosed (type 2 diabetes; hypertension) or with a physical or mental condition that would preclude their participation in physical activity program will be excluded from the study (analysis).

### Sample size calculation

The sample size estimation was conducted using G*Power (version 3.1) and based on detecting changes in the primary outcome of PA. Based on previous research, we anticipate the effect size for PA of d = 0.25 (an adjusted for the baseline of 5 min MVPA per day and assuming a standard deviation of MVPA of 17.8 minutes with a correlation of 0.59 between baseline and follow-up) [42]. We adjusted for clustering at the class level using a correction factor of [1 + (m—1) x ICC], where m represents the number of participants per class and ICC refers to the intraclass correlation coefficient for PA, assuming an average class size of 29 participating students, three classes per school and an ICC for PA of 0.034 [43]. Allowing for an expected dropout of 20% at the study endpoint, the required sample size to achieve 85% power with alpha levels set at 0.05 in 174 students (87 in the intervention group and 87 in the control group).

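### The 174 students do not give 85% power: the stated inputs require about 730 to 1,410, power at d = 0.25 is about 20%, and the abstract recruits only about 140

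*Protocol article*

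**What the plan says.** The section on sample size calculation in the protocol article gives these planning values:

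- Effect: "we anticipate the effect size for PA of d = 0.25", explained as "an adjusted for the baseline of 5 min MVPA per day", "assuming a standard deviation of MVPA of 17.8 minutes" and "with a correlation of 0.59 between baseline and follow-up".
- Clustering: a correction factor of 1 + (m − 1) × ICC at class level, "assuming an average class size of 29 participating students, three classes per school and an ICC for PA of 0.034".
- Dropout: 20% at the study endpoint.
- Result: "the required sample size to achieve 85% power with alpha levels set at 0.05 in 174 students", split 87 and 87.

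The abstract gives a different number: "The trial will aim to recruit ~140 adolescents".

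The section on blinding and randomisation makes the school the unit of allocation and plans two classes per school. The sample size section assumes three.

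**The concern.** The paragraph lists nearly every input of a standard two-arm calculation, so its result can be checked. An effect of d = 0.25 is small. It needs several hundred students even under individual randomisation, before a design effect that nearly doubles the number and a dropout allowance that adds a quarter. A total of 174 is far too low for that sequence. The stated d also does not match its parts, since 5/17.8 is 0.28, not 0.25.

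MVPA is the primary outcome. If the trial is reported as having 85% power for a gain of 5 min/day when its real power is a fraction of that, a non-significant result will be taken as evidence that the program does not work. The abstract adds to the problem: if about 140 is literally the number recruited, only 140 × 0.8 = 112 would be analysed.

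**Working it through.** **Inputs (all from the sample size section).** d = 0.25; difference 5 min/day; SD 17.8; r = 0.59; m = 29; ICC = 0.034; dropout 20%; power 85%; alpha 0.05; 1:1 allocation. Sidedness is not stated, so I assume two-sided and also give one-sided results. Sample sizes and power use the noncentral t distribution.

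**Step 1: attempt to reproduce 174.**

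- Design effect: 1 + 28 × 0.034 = 1.952.
- d = 0.25, 85% power: 289 per arm.
- After clustering: 289 × 1.952 = 564 per arm.
- After dropout: 564 / 0.8 = 705 per arm, about 1,410 in total.

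The plan's figure is not reproduced.

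**Step 2: other readings of the effect size.** Taken directly, 5/17.8 = 0.281. With baseline adjustment, the residual SD is 17.8 × √(1 − 0.59²) = 17.8 × 0.807 = 14.4, and d = 5/14.4 = 0.348.

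| d | per arm, no clustering | × 1.952 | / 0.8 | total |
|---|---|---|---|---|
| 0.25 | 289 | 564 | 705 | about 1,410 |
| 0.281 | 229 | 447 | 559 | 1,118 |
| 0.348 | 150 | 293 | 366 | 732 |

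The smallest total found, from a one-sided test at d = 0.348 with dropout applied as × 1.2, is about 560. Change-score, repeated-measures and paired versions were also tried, and no valid use of the stated inputs gives 174.

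**Step 3: power with 174 recruited.** After dropout, 87 × 0.8 = 69.6 per arm. Dividing by the design effect gives the effective number per arm:

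- 69.6 / 1.952 = 35.7 with m = 29.
- 69.6 / 1.755 = 39.7 if m is taken as completers per class (29 × 0.8 = 23.2, so 1 + 22.2 × 0.034 = 1.755).

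| d | two-sided power |
|---|---|
| 0.25 | 18–20% |
| 0.281 | 22–24% |
| 0.348 | 31–33% |

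With no clustering and no dropout at all, 174 students give about 38% at d = 0.25 and 63% at d = 0.348. The 85% therefore fails before either inflation is applied.

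**Step 4: detectable effect.** By the normal approximation, d = (1.960 + 1.036) × √(2/n) = 2.996 × √(2/39.7) to 2.996 × √(2/35.7) = 0.67 to 0.71. In minutes per day this is 9.7 to 10.2 with the adjusted SD of 14.4, and 12.0 to 12.6 with the unadjusted SD of 17.8.

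**Step 5: few clusters (an assumption).** Schools are randomised and their number is not given. If inference rested on about 4 cluster degrees of freedom, power would be about 13–14% at d = 0.25 and 21–22% at d = 0.348.

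**Step 6: the abstract.** 174 × 0.8 = 139, so about 140 may be the expected completers, but it is worded as the number to recruit. If 140 are recruited, power at d = 0.25 is about 15–17%.

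**Possible origin (inference only).** Entering 0.25 as Cohen's f, which equals d = 0.50 for two groups, gives 73 per arm, and 73 × 1.2 = 87.6, with no design effect. Equally, 3 classes × 29 = 87. The documents do not settle which applies, and the error does not depend on it.

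**The case against.** The strongest points on the other side concern the size of the shortfall, not its existence.

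- **How r = 0.59 enters.** The effect is described as baseline-adjusted, and the analysis plan names a repeated measures analysis of covariance. If d = 0.25 does not already include the gain from the correlation, power is higher than 20%. This stands, and it is why the range up to 33% is given. The figure of about 20% belongs to d = 0.25 as stated.
- **Sidedness.** A one-sided test would raise power, but to no more than about 46% in the best case.
- **Source of d.** It is credited to earlier research that cannot be seen here, and 17.8 may not be a cross-sectional SD. The mismatch between 0.25 and 5/17.8 therefore calls for the derivation to be shown. It does not prove that 0.348 is the right value.
- **Cluster degrees of freedom.** The value of 4 is not in the documents and the primary model uses class as its random effect. It is illustration only.
- **The abstract.** About 140 may be completers worded as recruits. That is plausible, but the two statements still conflict.
- **Condensed article.** Nothing is missing here that a fuller document could supply. The inputs and the result are both printed, and one does not follow from the other.

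**Conclusion.** The concern holds. On the plan's own inputs the requirement is about 1,410 students at d = 0.25, and 732 on the most favourable two-sided reading, against a stated 174. The trial as sized has about 20% power at the stated d and at most about a third under the best use of the baseline correlation, not 85%. The effect it could detect with 85% power is about 10 min/day of MVPA after baseline adjustment, double the 5 min/day planned for.

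These results assume a two-sided 5% test, the stated ICC and class size, and 20% loss in each arm. They are more likely optimistic than pessimistic, because the design effect covers classes only while whole schools are allocated. The recruitment figures in the abstract (about 140) and the sample size section (174) also contradict each other.

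**What to change.** Rewrite the sample size paragraph so that a reader can retrace it:

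1. Derive d from the 5 min difference, SD 17.8 and r = 0.59, and say whether it is baseline-adjusted (0.348 on the usual formula) or not (0.281). If 0.25 is kept, explain where it comes from.
2. State the sidedness and show the design effect and dropout steps one after the other. Use the same number of classes per school as the randomisation section.
3. Replace the 85% claim with what 174 delivers: power of roughly 20–33%, lower if there are few schools, or a detectable difference of about 10 min/day.
4. In keeping with that, present the primary comparison as estimation with a confidence interval, or as a pilot, so that a null result is not over-read.
5. Give one recruitment target in both places. If 174 is kept, write 174 recruited and about 139 expected to be analysed.

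The cost is text only. The stated power becomes much less favourable, but no extra students, measurements or changes to the program are required.

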### Blinding and randomisation

Randomization will occur among schools that have been recruited and have completed baseline assessments. The schools will be matched based on the following characteristics: school area-level socioeconomic status (i.e., using Socio-Economic Class ABEP) [44]. Schools will be randomised to either a control or an intervention condition by an independent researcher using a computer-based random number generator. We will aim to recruit two classes per school (ie, one class of 8 grade and another of 9 grade) (Fig 1). Schools selected to the intervention condition will participate in the program during the study period, whereas schools allocated to the control condition will continue usual school practice.

**Fig 1 pone.0272629.g001:**
[figure not shown]
Protocol timeline implemented for the study.

### Intervention

The ActTeens school-based PA program will be implemented over one school term (16-weeks) and will be designed to improve adolescents’ PA level, fitness, metabolic, and mental health. The *ActTeens Program* will include three major components: (1) structured PA sessions delivered within Physical Education, (2) self-monitoring plus goal setting by a pedometer, and (3) healthy lifestyle guidance (i.e., social support). The program will be guided by social cognitive theory [45] and self-determination theory (SDT) [46] and will target teachers, schools, students, and parents.

The structured PA sessions, which is focused on resistance training (RT) is an adaptation of Resistance Training for Teens [34]. RT for Teens was an Australian program designed to improve muscular fitness and provide adolescents with the knowledge, motivation, skills, and confidence to engage in resistance training. The structured PA sessions have been designed for satisfying participants’ basic psychological needs which include autonomy, competence and relatedness of the students, and so promoting autonomous motivation and self-efficacy for physical activity. The structured PA sessions was adapted from the earlier NEAT [38] and ATLAS programs [47]. The structured PA program will be delivered within PE lessons, twice a week, for 20-minutes per session (40 min·wk^-1^). The implementation strategies used to support adoption and delivery will include: (i) professional learning workshop for teachers; (ii) provision of teacher handbook, session resources, and fitness equipment; and (iii) physical activity session observation and feedback. The program will consist of the following components: (i) an introductory seminar for students delivered by teachers; and (ii) a structured PA program, focused on RT.

The introductory seminar will be designed to explain the rationale for the program and reinforce the importance of exercise for physical health (focus on muscular fitness), metabolic profile, and behavioral change such as physical activity self-monitoring and goal setting [47]. The structured PA sessions [34, 47] will follow a specifics format including i) movement-based games and dynamic stretching warm-up; ii) Resistance training skill development; iii) high-intensity workout, and iv) cool-down. Participants will be able to select from a variety of predesigned circuit cards, which will be released across the program to promote variety and sustain participant interest. The level of intensity for each session component will be guided by Borg´s CR-10 rating of perceived exertion scale.

To promote exercise adherence, sessions will be developed with a focus on enhancing students’ autonomous motivation [34, 47], within and beyond the school setting by satisfying their basic psychological needs for autonomy (feeling in control), competence (feeling capable), and relatedness (feeling connected with others) [46]. Teachers will learn to facilitate sessions using the Supportive, Active, Autonomous, Fair, and Enjoyable (SAAFE) teaching principles [48], which will serve as a framework for the design and delivery of the physical activity sessions, as well as session observations. They will be educated about the importance of and provided with strategies for, integrating SAAFE principles in their lessons during the professional learning workshop.

Participants’ need for autonomy will be satisfied by the teacher-delivery seminar and providing opportunities for choice within sessions (e.g., type of activity and preferred music playing). Competence will be satisfied using positive and specific feedback from teachers to enhance self-efficacy (e.g., providing encouragement, giving specific feedback on technique, modeling correct performance) [47]. Teachers will be encouraged to adopt practices that support relatedness and group cohesion during the sessions (i.e., encouraging supportive behavior among students) [48]. Several precautions will be undertaken to ensure the safety of participants including 1) explanation of correct technique for all exercises at the beginning of the program, whilst students are learning the techniques; 2) inclusion of warm-ups and cool-downs, and 3) reminders for teachers and research staff member to monitor and correct exercise technique.

Regarding the sessions, a range of sociocultural targeting strategies [49] will be applied to the program to increase relevance and appeal to adolescent boys and girls. For example, the circuit cards and interactive seminar will include images of female and male same-sex role models. In addition, the interactive seminar will include content that is relevant to boys and girls, separately and together, by recognizing and focusing on health behaviors common to each sex. However, the sessions will be conducted with mixed-sex groups.

To promote active behavior out of school, a pedometer plus goals setting will be used. Each adolescent within the intervention group will receive the researcher’s personalized goals (based on the number of steps measured in the baseline week), which must be achieved weekly. The goals will be predetermined way progressive [50], from the execution of an additional every two weeks 10% (first and the second week) to 45% (at week 15 and 16), and also will be sent by WhatsApp® messages to encourage adolescents to practice daily PA. Students and their parents will also be sent WhatsApp® messages about healthy eating and regular PA, to work toward improved healthy behaviors [51] (see Table 1 for further details of these strategies).

**Table 1 pone.0272629.t001:** Intervention and implementation description.

Component/Strategy	Dose	Description
Professional learning workshop	1x5-h workshop (preprogramme)	The workshop for PE teachers and research staff members will be delivered by principal investigator, which will be addressed all aspects of the intervention: 1) teacher roles and expectations; 2) intervention components; 3) introduction to active behavior, muscle strengthening and safety implications; and 4) philosophy of the programs, including the sex-targeting strategies and explanation of the ‘‘SAAFE” teaching principles.
Support from research team	Once per month	The research team will create an "intervention school" WhatsApp group and invite intervention´s teachers to join. The teachers will be encouraged to share challenges and successful strategies in the app.
Presentation to school staff	1x15 min	The research team will design a tailored presentation to the educational team (i.e., school principals, coordinators and school faculty) during a regularly scheduled staff meeting. The purpose of the presentation is to inform of the objectives and details of the programme, and to promote a supportive school climate.
Provision of teacher handbook, fitness equipment, and session resources, provided by the research team	Once	Schools will be provided facilitator handbooks, sets of circuit cards and fitness equipment packs.
Interactive seminar	1×1 hour seminar	Students will participate in an interactive seminar by a member of the research team. The interactive seminar will provide important information about the programme components and behavioural messages (including current recommendations for youth physical activity, healthy eating, screen-time). It will also address relevant information on physical, metabolic and mental health.
Structured physical activity program	2/week	The session will include bodyweight and elastic tubing resistance training, aerobic-based and strength-based activities, and high-intensity fitness challenges that will be run at school during physical education lessons for 16 weeks (2 times per week). Each exercise session will last approximately 20 min. Students will be able to select from a variety of pre-designed cards incorporating both aerobic-based and resistance-based exercises. Behavioural messages (i.e., be physically active, limit screen time, foods, and sugar-sweetened beverages) will be reinforced at the end of sessions (e.g., cooldown).
Pedometer plus goals setting	16-week	The pedometer plus goals setting will be used as a strategy to promote participation in PA of adolescents (out of school). Participants will wear Yamax SW700 pedometers for physical activity self-monitoring and will receive a new goal-setting (based on the number of steps measured in the baseline week) to achieve weekly. The goals setting will be progressive and changed every two weeks, and this strategy has as its objective propose a realistic goal setting aim to achieve at least 10000–11700 steps/day.
e-health	Twice per week	Adolescents of the intervention group will receive messages about healthy behavior (i.e, active lifestyle and healthy eating) by WhatsApp®.
Parental involvement	Once per week	Parents of intervention group students will receive weekly messages about the benefits of physical activity and healthy eating by WhatsApp® to support their adolescent’s healthy behavior change at home.

Adapted by Resistance Training for Teens program [34]–RT: Resistance training; IG: intervention group.

